### Study Aims and Hypotheses

This study will accomplish the following 3 aims:

#### Aim 1

We aim to assess the effect of a brief informational infographic about the scientific process on trust in science. *We hypothesize that exposure to such an intervention will have a moderate, positive effect on trust in science*.

#### Aim 2

We aim to assess the effect of a brief informational infographic about the scientific process on the likelihood of believing scientifically implausible narratives about COVID-19. *We hypothesize that exposure to such an intervention will have a small, negative effect on the likelihood of believing implausible narratives, as evidenced by profile membership, and that this will be partly mediated by trust in science*.

#### Aim 3

We aim to assess the effect of a brief informational infographic about the scientific process on behavioral intentions to engage in recommended COVID-19 NPBs. *We hypothesize that exposure to such an intervention will have a small, positive effect on behavioral intentions to engage in recommended COVID-19 NPBs that will be partly mediated by misinformation profile membership*.

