### Sample Size

We will recruit 1,000 individuals using Prolific, which is the maximum sample size permitted for a nationally representative sample via this platform. This sample size will give allow us to detect small (Cohen’s d=0.18) differences between both groups with 80% power. This effect size would be more than sufficient for both analysis types, that is, LMM (linear mixed models) and path analyses, thus accounting for power and other sample size considerations common to path analysis (eg, overspecification) [61].

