### Allocation of Interventions

The allocation sequence will be managed using the Randomizer tool in the Qualtrics platform [62] to ensure a 1:1 allocation of participants to intervention (1) and control (0) arms, each comprising 500 participants. Allocation will occur after consent has been processed. Furthermore, the procedure is automated, thereby ensuring allocation concealment.

Although this is, in practice, a double-blind study since participants will be unaware that they are randomized and all study mechanics will be processed using a computer, analysts will not be blinded to the meaning of the assignment variable. However, 2 independent consultant analysts have been retained to verify all results and subsequent interpretation.

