#### Analyses

The following analyses will be performed for the 3 aim statements:

**Aim 1**: We will use an LMM to examine the effect of the intervention on trust in science, controlling for specified covariates (see Covariates).

**Aim 2**: We will first examine the profiles of believability in our control and intervention group using latent profile analyses [65,66]. After determining the number of classes and identifying scientific versus nonscientific profiles, we will conduct path analyses linking the brief digital intervention to believability profiles and the mediator (trust in science).

**Aim 3**: We will first examine the outcome variables for Aim 3—intention to engage in NPBs. Although we expect these intention-based items to function as a monotonic scale that can be collapsed into a single variable, we will need to conduct exploratory factor analysis to determine whether this is the case. The number of factors identified will affect how this outcome is treated in the subsequent part of Aim 3.

We will also examine the mediation effect of believability profiles on the association between behavioral intentions, trust in science, and the primary outcome for Aim 3 (ie, intention to engage in NPBs) in the post-test. Next, we will conduct path analyses linking the brief digital intervention to believability profiles and the mediators (trust in science and believability profiles), and behavioral intentions in the post-test.

For both Aims 2 and 3, we will use model fit statistics (eg, root mean square error of approximation, comparative fit index, and Tucker-Lewis Index) and examine specific indices of ill fit (eg, modification indices). To increase power and maintain Type I error, we will adapt the posterior probability method (eg, partial *P* value) for formal mediation analyses with intervening variables [67]. We aim to elucidate key mediational chains between our mediators (ie, trust in science and believability classes), predictors (ie, behavioral intervention statement), and outcome (ie, intention to engage in NPBs) through this design, instead of simply looking at the link between the intervention and intention to engage in NPBs.

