### Study Limitations

This study has several limitations that might affect its conclusions. First, the data are based on self-reporting. For believability and trust in science, this is a less substantive issue; however, it is potentially subject to social desirability bias, which we will attempt to minimize. Although extant behavior models like the Theory of Planned Behavior [59] indicate that intentions are direct antecedents to behavior, we cannot be certain that intentions will result in actual behavior. Nevertheless, measuring this would be beyond the scope of this protocol. Second, we are unable to control the conditions in which people will participate, but we will incorporate attention checks throughout the process. Furthermore, prior studies have been able to replicate known experimental findings using crowdsourced digital participants, suggesting that the undue influence of inattention can be minimized [42,43]. Third, this experimental approach is likely subject to a Type II error because a real-life application of this process would entail repeated exposures over time, whereas this approach tests the effect of a single exposure. Fourth, other variables that might influence behavioral intentions also likely exist, but by recruiting a large sample and randomizing participants, we will be able to more cleanly isolate the differences attributable to the intervention.

Finally, generalizability to individuals who do not have internet access or who are unable to participate in online surveys might be limited. However, regarding the concern about access, it is noteworthy that approximately 90% of US adults used the internet in 2019, with higher percentages reported for younger adults and lower percentages, for older adults. Of note, 73% of individuals aged >65 years reported they had internet access in 2019 (although it began trending sharply upward in 2018) [70]. Furthermore, as noted throughout our proposal (and in academic papers published since submission [71]), social media remains a primary source of misinformation about COVID-19. Considering that the online data collection platform introduces bias as a result of internet access, we speculate that controlling for age (which we already do) may attenuate this concern to an extent, in addition to the fact that the intervention itself is designed for distribution on social media.

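### The mediation tests for Aims 2 and 3 maintain Type I error against sampling error only; they control false mediation findings only if no unmeasured mediator-outcome confounding remains, a condition the article does not state

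*Protocol article*

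**What the plan says.** Study Aims and Hypotheses makes mediation part of two hypotheses. For Aim 2, the effect on profile membership is expected to be small, and "this will be partly mediated by trust in science". For Aim 3, the effect on intentions is expected to run partly through profile membership. Aim 1 supplies the first link: "exposure to such an intervention will have a moderate, positive effect on trust in science".

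The Analyses section plans path models for Aims 2 and 3 and a partial P value test of the indirect effects. It gives the reason: "To increase power and maintain Type I error, we will adapt the posterior probability method". It then states the purpose: "We aim to elucidate key mediational chains between our mediators", the predictor and the outcome, in preference to looking only at the link from intervention to intentions.

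On measurement, Trial Design says the whole trial takes place in one session, and Study Limitations says the data are self-reported. Trust is measured before and after exposure. Believability and intentions are measured only afterwards. The Covariates section lists measured adjustment variables; pre-exposure trust is not among them, and the Analyses section does not say that it enters the path models.

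**The concern.** Randomizing the infographic protects its effect on trust, on profile and on intentions. It does not protect the trust-to-profile path or the profile-to-intention path, because nobody is randomized to a level of trust or to a profile. Response style, social desirability or an unmeasured attitude could move two of these self-reports together. The mediator-to-outcome coefficient would then differ from zero even if the mediator did nothing. A test of the product of paths treats that coefficient as causal.

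The article's own background shows why this matters. In the team's earlier cross-sectional work, each 1-point decrease in trust went with 5 to 14.3 times higher adjusted odds of a nonscientific profile. A significant trust-to-profile path is therefore likely whether or not trust is the cause. What is at stake is whether the partly-mediated elements of Aims 2 and 3 could be reported as supported when no causal chain exists. The randomized effects themselves are not in question.

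**Working it through.** **Inputs from the article.** Sample Size: "We will recruit 1,000 individuals using Prolific". Allocation of Interventions: two arms, "each comprising 500 participants". Sample Size: d = 0.18, "differences between both groups with 80% power". Conceptual Framework: about 70% of respondents in the scientific profile.

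**Assumptions.** The article gives no alpha, so two-sided 5% is used. It gives no number for a moderate effect, so d = 0.5 is used next to d = 0.18. It gives no residual correlation (rho), so a range is shown.

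**1. The plan's own figure.** n per arm = 2(1.96 + 0.842)²/0.18² = 485, or 970 in total. At 500 per arm the test statistic has mean 0.18 × √250 = 2.85, which gives 81.2% power. The detectable d at exactly 80% power is 0.177. The stated figure is reproduced. It concerns a between-group difference, not an indirect effect.

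**2. Model with no mediation.** X is arm, M = d·X + e_m, Y = 0.18·X + e_y, and corr(e_m, e_y) = rho is the correlation left after covariates. M has no effect on Y.

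**3. Closed form for the joint-significance test** (both paths significant), at d = 0.18 and rho = 0.10:
- Arm-to-mediator path: mean statistic 2.85, probability 0.812.
- Mediator-to-outcome path: mean statistic rho·√N/√(1 − rho²) = 0.10 × 31.62/0.995 = 3.18, probability 0.888.
- Product: 0.812 × 0.888 = 0.72.

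The second statistic grows with √N, so a larger sample raises this rate.

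**4. Simulation of an approximate partial P value test.** With t_a and t_b the two path statistics and T = |t_a·t_b|, average 2[1 − Φ(T/|t_b + z|)] over standard normal z, do the same with t_a in place of t_b, and take the larger average as the P value. There were 1,000 trials per cell with N = 1,000. The table shows how often mediation is declared when none exists.

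| Mediator | d on mediator | rho 0 | 0.05 | 0.10 | 0.20 |
|---|---|---|---|---|---|
| Continuous | 0 | 0.2% | 0.4% | 2.2% | 5.3% |
| Continuous | 0.18 | 2.2% | 22% | 65% | 80% |
| Continuous | 0.5 | 4.4% | 37% | 90% | 100% |
| Binary 70/30 | 0.18 | 2.2% | 7% | 27% | 54% |
| Binary 70/30 | 0.5 | 5.1% | 17% | 59% | 99.5% |

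For the binary rows, d is the shift on the latent scale before the cut. The binary row with d = 0.18 is the closest match to Aim 3, where the mediator is the profile and the expected effect on it is small. The continuous rows stand for trust as mediator. They use a continuous outcome, whereas the Aim 2 outcome is profile membership, so they are indicative for Aim 2 rather than exact.

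**5. Adjusting for pre-exposure trust.** A side run let a stable unmeasured trait drive both trust and the outcome, with an assumed reliability of 0.9 for trust and the joint-significance test. The ranges cover d = 0.18 and d = 0.5.
- Implied rho √0.9 × 0.2² = 0.038: 18–23% unadjusted, about 5–6% adjusted.
- Implied rho √0.9 × 0.3² = 0.085: 63–77% unadjusted, 8–10% adjusted.
- Implied rho √0.9 × 0.4² = 0.152: 83–99.8% unadjusted, 19–20% adjusted.

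This run covers stable traits only. Adjustment for baseline trust cannot remove correlation that arises after exposure in the same session. The profile has no baseline of its own to adjust for.

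**The case against.** A reader might infer several stronger points that the article does not support.

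- *That the Type I error sentence is false.* It is not. Read as a reason for choosing one indirect-effect test over another, it concerns sampling error, and at rho = 0 the test kept about 5% or less. What happens at rho above zero is confounding bias, and the article does not claim that the test removes it.
- *That nothing guards against shared causes.* The Covariates section includes political orientation, religious commitment, COVID-19 history, perceived severity, self-efficacy and normative beliefs, all plausible common causes. Trust is measured before exposure, measurement error is to be explored, and social desirability is named as a limitation to be minimized.
- *That mediation would be declared whenever the self-reports correlate slightly.* At rho = 0.05 the rates at d = 0.18 are 7% and 22%. The infographic must also move the mediator; for Aim 3 that means the profile, not only trust.
- *That Study Limitations wrongly relies on randomization.* The sentence "by recruiting a large sample and randomizing participants, we will be able to more cleanly isolate the differences attributable to the intervention" is about the arm effect, which randomization does protect. It makes no claim about mediator-to-outcome paths.

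It can also be said that a sensitivity analysis for mediation belongs in a statistical analysis plan, which is not shown. That is fair, and its absence from the article is not itself the fault. What remains is that the article asserts an error property for formal mediation tests and makes mediation part of two hypotheses without naming the condition on which the causal reading depends. The planned covariates reduce rho, but nothing in the article shows that they bring it to zero.

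**Conclusion.** The point holds as a limit on what the mediation results can support. The stated Type I error control covers sampling error. It extends to false mediation findings only if no unmeasured mediator-outcome confounding remains after covariates. With d = 0.18 on the mediator and modest residual correlations, the false-mediation rate is about 7% to 54% for a binary profile and 22% to 80% for a continuous mediator. It is higher if the effect on the mediator is larger.

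These figures rest on assumed values of rho, of alpha and of the effect on the mediator, and on simplified single-mediator models. Pre-exposure trust, if entered in the path models, would lower the rate for the trust mediator considerably. If the infographic does not move the mediator, there is no material inflation. Nothing here weakens the randomized comparisons, and nothing requires mediation to be ranked below them or made to pass a fixed correlation threshold.

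**What to change.** Keep the path analyses and make four changes.

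1. Include pre-exposure trust as a covariate in the Aim 2 and Aim 3 path models.
2. Amend the sentence to say that Type I error is maintained under no unmeasured mediator-outcome confounding.
3. Prespecify a sensitivity analysis for each indirect effect. Fix the mediator-outcome residual correlation at values over a range, for example −0.3 to 0.3, re-estimate, and report the value at which the effect becomes zero or non-significant. A residual correlation is not directly defined for a profile with several classes, so use the scientific/nonscientific split on a latent scale for this purpose.
4. Describe any mediation finding as conditional on that assumption.

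No new data are needed. The cost is a little more analysis work, including setting up the latent-scale version for the profile, and more cautious mediation conclusions.

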## Results

This study was funded in August 2020, approved by the Indiana University Institutional Review Board on September 15, 2020, and prospectively registered with ClinicalTrials.gov. We expect the infographics to be finalized in early December 2020 and plan to run the pilot test in the same month. The entire experiment should be completed, and the results published, in 2021. This protocol was submitted as prepared for review in a grant format to the Indiana Clinical and Translational Sciences Institute in June 2020. Aside from stylistic modifications made in transforming the grant into a paper, and in addressing grant reviewers’ and manuscript reviewers’ comments, the protocol reflects the originally proposed work.

## Discussion

### Next Steps

The primary purpose of this study is to test an actionable, brief digital intervention that can modify trust in science and thereby mitigate belief in misinformation and increase behavioral intentions to engage in NPBs. Thus, if any hypotheses are validated, the primary next step will be to disseminate this information and coordinate use of the infographic. Two articles published in *Nature* [68,69], (including one by that journal’s editorial board), acknowledged the need for researchers to honestly and transparently address COVID-19 misinformation, and to specifically look into trust, but the cited research primarily examined networking and spread dynamics, not prevention.

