Specifically, we will expand on current knowledge by assessing whether exposure to a brief informational statement (in the form of an infographic) about the scientific process can increase trust in science, reduce the likelihood of believing scientifically implausible narratives about COVID-19, and increase intentions to engage in recommended COVID-19 NPBs. Given the scale and scope of the pandemic, an intervention with a small effect size, if feasible to deploy within the cost-effective US social media infrastructure, would have the potential to save lives through increased adherence to NPBs. However, it is important not to rush the deployment of brief social media campaigns without careful research and planning to verify efficacy, given that such campaigns could have iatrogenic effects even when designed by scientists and media experts [34,35]. This echoes the recent findings by Lane and Fauci [36], who remind researchers even in the context of a pandemic, it is important to generate scientifically sound evidence.

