### Primary Study Outcomes

#### Trust in Science

Participants’ “trust in science” will be measured both before and after they view the intervention or placebo using the 21-item scale developed by Nadelson et al [37]. Our previous research has found that this scale is highly reliable for diverse, online, and crowdsourced respondents [17,21].

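### Dissemination is to follow if any of three unranked primary hypotheses is supported, and no error control spans the three aims

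*Protocol article*

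**What the plan says.** The Methods section headed "Primary Study Outcomes" covers three outcomes: trust in science, believability profiles and behavioral intentions. None is placed above the others.

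Study Aims and Hypotheses attaches a directional hypothesis to each:

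- Aim 1: "exposure to such an intervention will have a moderate, positive effect on trust in science".
- Aim 2: "exposure to such an intervention will have a small, negative effect on the likelihood of believing implausible narratives, as evidenced by profile membership", with a further clause that trust in science partly mediates this effect.
- Aim 3: a "small, positive effect on behavioral intentions to engage in recommended COVID-19 NPBs that will be partly mediated by misinformation profile membership".

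The Analyses section gives each aim its own analysis ("The following analyses will be performed for the 3 aim statements"). For Aim 3, an exploratory factor analysis will decide whether the intention items form one outcome or several. The same section holds the only statement on error control: "To increase power and maintain Type I error, we will adapt the posterior probability method". It applies to the formal mediation analyses.

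Under Next Steps in the Discussion, the consequence of a positive result is that "if any hypotheses are validated, the primary next step will be to disseminate this information and coordinate use of the infographic".

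**The concern.** When one success among several is enough to act, the error rate that matters is the chance of at least one false success. The mediation provision does not limit that rate. It leaves out Aim 1 and the direct arm effects, and it does not deal with having three primary hypotheses.

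The power statement does not suggest a divided alpha either. It describes a single two-group difference, and its figure fits an unadjusted test.

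The consequence matters by the article's own standard. The Introduction raises the possibility of iatrogenic effects and says that "it is important not to rush the deployment of brief social media campaigns without careful research and planning to verify efficacy". As worded, the Next Steps sentence would allow roll-out on an isolated result in intentions with no effect on trust, although the stated mechanism runs through trust.

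**Working it through.** **Inputs from the article.** 1000 participants, 1:1, 500 per arm (Sample Size; Allocation of Interventions); d=0.18 at 80% power (Sample Size); three primary outcomes with directional hypotheses.

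**Assumptions.** Alpha is not stated, so two-sided 0.05 per arm contrast is assumed. The correlation between the three test statistics is not given, so it is varied from 0 to 0.9.

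**Step 1: reproduce the stated power.** Detectable d = (1.960 + 0.842) × √(2/500) = 0.177, which rounds to the stated 0.18. Power at d=0.18 is 81.2%. One-sided 0.05 would give a detectable d of 0.157 and power of 88.5%, which does not match. The stated figure therefore fits one comparison at an unadjusted two-sided 0.05.

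**Step 2: at least one significant arm contrast when the infographic does nothing.** If independent:

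- either direction: 1 − 0.95³ = 14.3%;
- in favor of the infographic only: 1 − 0.975³ = 7.3%.

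For correlated statistics, three equicorrelated normal statistics were simulated with 1,000,000 draws:

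| Correlation | Either direction | Favorable only |
|---|---|---|
| 0 | 14.3% | 7.3% |
| 0.3 | 13.6% | 6.8% |
| 0.5 | 12.5% | 6.3% |
| 0.7 | 10.9% | 5.5% |
| 0.9 | 8.4% | 4.2% |
| One test alone | 5% | 2.5% |

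The hypotheses are directional and an adverse result would not support any of them, so the favorable-only column is the one that measures mistaken dissemination. The excess over nominal is 4.2/2.5 = 1.7-fold to 7.3/2.5 = 2.9-fold. The outcomes lie on one proposed causal chain, so positive correlation is likely and the zero-correlation row is an upper figure for three tests.

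**Step 3: the stricter reading of Aims 2 and 3.** Suppose that Aim 2 counts as supported only if the trust contrast is also significant, and Aim 3 only if the profile contrast is also significant. Support for Aim 2 then adds nothing beyond Aim 1, and a false success needs trust, or else both profiles and intentions. If independent, this is 0.05 + 0.95 × 0.05² = 5.2% in either direction, or 0.025 + 0.975 × 0.025² = 2.6% favorable only. Over correlations 0 to 0.9 the ranges are 5.2% to 5.8% and 2.6% to 2.9%. Requiring a significant first path only approximates the planned partial P value method, so these figures are illustrative.

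**Step 4: what an equal alpha split would cost.** At 0.05/3 per outcome, detectable d = (2.394 + 0.842) × √(2/500) = 0.205. Power at d=0.18 falls to 67.4%, and 647 per arm (1294 in total) would be needed to restore 80%. The article gives 1000 as the platform's maximum.

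**The case against.** Four objections deserve an answer.

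**The 14.3% overstates the harm.** A reader might infer that an inert infographic has about a one-in-seven chance of being rolled out. The documents do not support that. The hypotheses are directional, and 14.3% counts adverse results and assumes independence. The favorable-only range is 7.3% to 4.2%, so even a flat statement that the chance exceeds 5% fails at correlation 0.9. This objection stands in full.

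**Aims 2 and 3 are not stand-alone contrasts.** Both hypotheses include a mediation clause. If the whole sentence must hold before a hypothesis counts as supported, the inflation nearly disappears (Step 3). This stands as a possible reading. The article does not say whether the arm effect alone would be enough, so the reading neither proves nor removes the problem.

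**Next Steps is not a success criterion, and the analysis plan is not shown.** The sentence sits in the Discussion, and adjustment details are commonly left to an analysis plan. Silence on multiplicity would indeed be no finding. The point rests on the rule that the article itself writes down, which joins action to any one hypothesis. The placement lowers the weight of the point but does not remove it.

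**The split of intentions is hypothetical.** The article expects a single scale and does not say that several factors would each be tested without adjustment. A reader might infer a certain further rise in error, but the text supports only that the number of Aim 3 outcomes is open. Four independent tests would give 1 − 0.95⁴ = 18.5% in either direction, purely as an illustration.

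**Conclusion.** The concern holds in moderate form. Three unranked primary hypotheses are joined by an any-success rule for dissemination, and the one Type I error provision does not reach across them. At an assumed two-sided 0.05 per arm contrast, the chance that an inert infographic produces at least one favorable significant result is 7.3% if the tests are independent, falling to 4.2% at correlation 0.9, against 2.5% for one test. In either direction it is 14.3% falling to 8.4%. If Aims 2 and 3 need their mediation clauses as well, the favorable figure is only about 2.6% to 2.9%. The article does not settle which reading applies, and that ambiguity is part of what should be corrected. The change should be made, but the point does not undermine the design.

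**What to change.** 1. Test the arm effects in a fixed sequence that follows the plan's own causal order: trust in science, then profile membership, then intentions. Test each at two-sided 0.05, and stop confirmatory claims at the first non-significant result. This holds the family-wise error at 5% whatever the correlation, provided each step is a single test.
2. If the factor analysis yields more than one intention factor, apply Holm across the factors within the third step.
3. Treat the mediation tests as secondary, so that confirming an aim refers to its arm effect.
4. Reword the Next Steps sentence so that dissemination follows hypotheses confirmed in that sequence, not any hypothesis.

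This takes about a paragraph and no new data. Alpha is not divided, so the d=0.18 at 80% power figure for Aim 1 is unchanged. The cost is that Aims 2 and 3 become exploratory if Aim 1 misses. If the investigators will not accept that, naming one primary outcome or splitting alpha would also control the error. The split carries the power loss shown in Step 4, at a sample size that the platform does not allow to grow.
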